# Objectives

This study is a randomized, double-blind, placebo-controlled, parallel, multi-center, investigator-initiated clinical trial to assess the efficacy, safety, and economic value of OJS plus SMS compared to placebo in patients with GERC.

# Participants

## Inclusion Criteria

1. Aged 19-65 years
2. Subjects who have had a history of cough continuously for > 8 weeks
3. Subjects who had been diagnosed with GERD within the last 1 year (those who submitted documents diagnosed with reflux esophagitis at other hospitals or prescribed reflux esophagitis medicines for more than 4 weeks)
4. Subjects who consent to participate

## Exclusion Criteria

1. Present with abnormal findings on chest radiography, pulmonary function test, or nasal endoscopy that might lead to cough.
2. Diagnosis of acute respiratory diseases (including upper respiratory tract disorders) within the previous month.
3. Presence of postnasal drip syndrome
4. Diagnosis of chronic respiratory diseases (e.g., chronic obstructive pulmonary disease, bronchial asthma, bronchiectasis, interstitial lung disease, and other chronic respiratory diseases) within the last 2 years
5. Diagnosed with Los Angeles classification system grade C or higher GERD within the past year
6. Symptoms indicative of malignant disease within the GI tract (e.g., severe dysphagia, bleeding, weight loss, anemia, and bloody stools)
7. History of esophagostenosis, esophageal varices, Barrett’s esophagus, peptic ulcer or gastrointestinal bleeding, and Zollinger-Ellison syndrome.
8. History of surgical or endoscopic anti-reflux treatment
9. Treatment with angiotensin-converting enzyme inhibitor during the previous 4 months
10. Treatment with cough medicines, glucocorticoids, leukotriene receptor antagonists, anticholinergic drugs, long-acting β2-agonists within the previous 2 weeks
11. Treatment with antihistamines within the previous 2 weeks
12. Treatment with PPIs, histamine receptor antagonists, mucosa-protective agents, GI motility promoters, antacids, antidepressants, anxiolytics, and lower esophageal sphincter agonists within the previous 2 weeks
13. Treatment with digitalis, mineralocorticoids, anticoagulants, and high-dose aspirin (≤325 mg is allowed) within the previous 4 weeks
14. Treatment with potassium-containing drugs, licorice-containing drugs, glycyrrhizinic acid or its salt-containing drugs, loop diuretics (furosemide, ethacrynic acid), or thiazide diuretics (trichloromethiazide) within the previous four weeks
15. A lifetime smoking history of ≥20 packs (400 cigarettes)
16. Body mass index < 18.5 kg/m^2^
17. Aspartate aminotransferase (AST) or alanine aminotransferase (ALT) level at least twofold higher than the upper limit of normal or an eGFR ≤ 60 mL/min/1.73㎡
18. Unregulated hypertension (high blood pressure of 160 mmHg in the condenser or high blood pressure exceeding 100 mmHg in a relaxation period > 3 min)
19. Active infection requiring systemic antibiotic therapy
20. Blood-clotting disorder
21. Hepatitis B (active) or hepatitis C, chronic liver disease
22. History of cerebrovascular accident (CVA)
23. History of malignant tumors (e.g., lung or esophageal cancer) within the last five years
24. History of drug or alcohol abuse
25. Allergies or sensitivities to the experimental medicine/placebo
26. Pregnant or breastfeeding
27. Subjects who did not agree to use contraception by medically permitted methods
28. Subjects who have participated in clinical trials within the past month
29. Subjects who are judged by the investigators to be inappropriate for the clinical trial

## Sample size

1. **Sample Size**

| OJS plus SMS group | Placebo group | Total |
| --- | --- | --- |
| 69 | 69 | 138 |

1. **Rationale**

Based on our previous study results, we calculated a sample size of 138 (69 participants for each group) for this trial (16). The calculation was conducted to test the difference in the change in CDS from baseline (week 0) to post-dosing of OJS plus SMS (week 6) compared with the placebo. In our preliminary clinical trial, the mean difference between the two groups was found to be 0.75 and the standard deviation was 1.4. We assumed the power to detect the difference to be 0.8, the two-sided significance level to be 0.05, and a dropout rate of 20% to determine the sample size.

## Recruitment

Participants will be recruited from the outpatient departments of Pulmonology or Gastroenterology at each affiliated hospital. Recruitment brochures will be posted on the bulletin boards and websites of each hospital, and advertisements in mass media or local communications will be conducted as needed to promote recruitment.

# Trial Design

## Procedure

This study is a randomized, double-blind, placebo-controlled, parallel, multi-center, investigator-initiated clinical trial to assess the efficacy, safety, and economic value of OJS plus SMS compared to placebo in patients with GERC. The trial will be conducted at five hospitals in South Korea: Kyung Hee University Korean Medicine Hospital, Gangdong Kyung Hee University Korean Medicine Hospital, Daejeon University Daejeon Korean Medicine Hospital, Pusan National University Korean Medicine Hospital, and Catholic Kwangdong University International St. Mary's Hospital. After participants voluntarily signed a written informed consent, they will be screened for eligibility assessment, and those who meet the inclusion criteria will be enrolled for the next 8 weeks of the trial period (Fig.1). A total of 138 participants will be enrolled in this study from January, 2024. Participants will be allocated to either the OJS plus SMS group or the placebo group in a 1:1 ratio and will be asked to administer the investigational medicine three times a day for 6 weeks. For the evaluation of efficacy, safety, and economic assessments, participants will visit every 2 weeks until the last follow-up visit on week 8.

[figure not shown]

<임상시험 진행 흐름>

## Randomization and Blinding

An independent statistician conducted randomization using a computer random number generator of SAS® Version 9.4 (SAS institute. Inc., Cary, NC, USA) using the block randomization method. The allocation ratio was 1:1 for each intervention (OJS plus SMS) and control (placebo) group. The generated random sequence was transmitted to the manufacturer responsible for labeling the participants’ identification codes on each investigational medicine package. These labelled medicines will be delivered to management pharmacists at each hospital, and pharmacists will give the corresponding investigational medicine to each participant using their identification code. The random number will be kept by an independent investigator who has no relationship with the patient throughout the trial and will only be disclosed when a serious adverse event occurs.

All investigators, participants, and outcome assessors will be blinded. The intervention and placebo drugs are distinguished only by the participants’ identification codes, labelled in identical and opaque packages, and both drugs were manufactured with the same color, taste, and smell.

# Dropout and Early termination criteria

At any time during the clinical trial, participants can voluntarily withdraw from the clinical trial. Additionally, anyone who meets any of the following conditions will be dropped out from the trial at the discretion of investigators:

1. found to violate the inclusion and exclusion criteria after screening visit,
2. in the case where the participant requests discontinuation of the trial or refuses the treatment due to unsatisfactory treatment effects during the trial period,
3. in the case where the participant cannot be tracked during the trial period,
4. when it is judged by investigators that trial participation is no longer possible due to an adverse reaction or a concomitant disease,
5. in the case of taking prohibited drugs that may affect the trial result without the instruction of investigators during the trial period,
6. when it is judged that the effect evaluation of the clinical trial is not appropriate because the overall compliance with the investigational products is less than 70% in YGJ and PWS groups,
7. when the participant violates the trial plan, and it is difficult for the participant to continue the trial, and
8. when investigators judged that the progress of the clinical trial is no more appropriate.

In principle, this clinical trial is finalized when the registration of the planned number of participants is completed and the completeness of the collected data is secured. However, in the following cases, this clinical trial can be discontinued: (1) when the harmfulness of the supplied investigational products is found, (2) if moderate or severe adverse events judged to be related to investigational products occur in more than 25% of all participants, and (3) in the case when the targeted participants are not registered even though a sufficient recruitment period has been given.

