# Statistical analysis

Statistical analysis will be performed by an independent statistician using SAS Analytics Pro software and significance will be accepted at an α-level of 0.05 in a two-sided test. For all data analyses, full analysis (FAS) set will be the primary analysis set in this trial, and a per-protocol (PP) set will be performed as an additional analysis. In this trial, the FAS set included all randomly assigned participants who had been evaluated for efficacy at least once after the administration of the investigational medicine. PP sets were defined as participants who completed the trial without violating the protocol, with compliance lower than 75%, taking prohibited medications, or presenting with serious adverse events. Continuous variables are presented as means and 95% confidence intervals and categorical variables as frequencies and percentages.

For primary efficacy analysis, the changes in CDS between baseline and week 6 of OJS plus SMS compared with placebo will be evaluated using a mixed-effect model repeated measure (MMRM), with each group and visit set as fixed effects and participants as random effects. Secondary efficacy analysis, comparing cough VAS, LCQ-K, GERDQ, HARQ, and EQ-5D-5L evaluated at each visit point with baseline between groups, will also be performed using MMRM. The analysis of the changes in each efficacy outcome within the group will be performed using a paired t-test or Wilcoxon signed-rank test, depending on its normality. For missing values, a multiple imputation will be performed. Additionally, to analyze the trends of CDS over time compared with the baseline, RM-ANOVA will be conducted, and Dunnett’s procedure (based on the baseline) will be used as a multiple comparison correction. A safety analysis will be conducted to compare the number of adverse events between groups using Fisher’s exact test.

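### The dropout rules do not separate stopping study drug from leaving the trial, so participants can lose their week-6 CDS for reasons related to outcome when it could have been collected

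*Protocol*

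**What the plan says.** In the protocol, Dropout and Early termination criteria, the consequence of meeting a listed condition is removal from the trial, not only from treatment: "anyone who meets any of the following conditions will be dropped out from the trial at the discretion of investigators". Four of the eight conditions matter here:

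- Item 1: ineligibility discovered after the screening visit.
- Item 2: a request to stop the trial, or a participant who "refuses the treatment due to unsatisfactory treatment effects during the trial period".
- Item 5: "in the case of taking prohibited drugs that may affect the trial result without the instruction of investigators during the trial period".
- Item 6: overall compliance below 70%, where the effect evaluation is judged inappropriate.

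Primary Efficacy Outcome defines the endpoint as the change in CDS from baseline to week 6, taken from a twice-daily home diary averaged between visits. Statistical analysis makes the FAS the primary set: all randomised participants with at least one efficacy evaluation after dosing. The model is MMRM, and on gaps the section says only: "For missing values, a multiple imputation will be performed". It gives no imputation model and no missing-data assumption. A per-protocol set, which screens on compliance and prohibited medication, is an additional analysis. No section describes diary or visit collection after a participant has been dropped.

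**The concern.** Stopping or deviating from study drug is an event after randomisation. It does not by itself prevent the participant from filling in a diary. The protocol treats it as a reason to end participation, and the listed reasons are not neutral. Lack of effect is close to the outcome itself. The prohibited drugs in question are by the protocol's own description ones that may affect the result, and the pre-entry exclusions include cough medicines and PPIs, which a participant who is still coughing may seek.

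Item 6 is in substance a reason for an analysis set: it removes people because evaluating effect in them is thought inappropriate. The per-protocol set already serves that purpose. Applied to data collection, the same reason also takes week-6 data away from the FAS.

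What is at stake is whether the primary comparison can be read as a comparison of the groups as randomised. An analysis plan can choose how to model missing values, but it cannot recover diaries that were never kept. Early loss also removes EQ-5D-5L and cost data from the 8-week economic evaluation.

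**Working it through.** **1. Reproduce the planned sample size.** The inputs are all in Sample size. From the pilot, "the mean difference between the two groups was found to be 0.75 and the standard deviation was 1.4". The same section sets 80% power, a two-sided 5% test and 20% dropout.

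- n per arm = 2 × [1.4 × (1.960 + 0.842) / 0.75]² = 54.7, rounded up to 55.
- Inflation for dropout: 55 / 0.80 = 68.75, rounded up to 69 per arm, 138 in total. This matches the protocol.

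The calculation therefore counts 20% of participants (0.20 × 138 = 27.6, about 28) as lost and takes the full 0.75 as the effect in the 55 per arm who remain.

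**2. Trace what happens to a participant who meets a condition.**

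| Step | What the protocol provides |
| --- | --- |
| Meets item 1, 2, 5 or 6 | Removal from the trial, at investigator discretion |
| Diary and visits afterwards | Nothing planned |
| Removed before any post-dose evaluation | Outside the FAS |
| Removed after week 2 or week 4 | In the FAS with the values to that point; week-6 CDS missing |
| Judged non-compliant at visit 5 (week 6) | Week-6 diary may already be in; value need not be lost |
| Missing week-6 CDS | Multiple imputation, assumption not stated |

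Under missing at random, MMRM and standard multiple imputation predict the missing week-6 value from participants with similar earlier CDS who stayed. If someone leaves because the drug has stopped working, or has started another cough drug, the earlier CDS need not carry that information.

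**3. What follow-up would do to the effect and to power.** The assumptions here are not in the protocol: a fraction d leaves in each arm; the effect is 0.75 in those who stay; leavers keep a fraction r of the benefit; the SD stays at 1.4; and all 69 per arm are followed.

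- Effect in all randomised = 0.75 × (1 − d) + 0.75 × r × d.
- Power = Φ( effect / (1.4 × √(2/69)) − 1.960 ), where 1.4 × √(2/69) = 0.238.

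| d | r | Effect | Power, 69 per arm | n per arm with data for 80% |
| --- | --- | --- | --- | --- |
| 10% | 0.5 | 0.7125 | 85% | 61 |
| 10% | 0 | 0.675 | 81% | 68 |
| 20% | 0.5 | 0.675 | 81% | 68 |
| 20% | 0 | 0.60 | 71% | 86 |
| 30% | 0.5 | 0.6375 | 76% | 76 |
| 30% | 0 | 0.525 | 60% | 112 |

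For reference, by the same formula, power is 80.2% with 55 per arm and an effect of 0.75. It is 88.2% with 69 per arm only if the effect is 0.75 in everyone, leavers included. Full follow-up equals the planned power when the effect is 0.75 × √(55/69) = 0.67; below that, power falls short of the plan.

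**4. Distance between the two targets.** If leavers were imputed as though they had stayed on treatment, the estimate would aim at 0.75. At d = 20% that exceeds the effect in all randomised by 0.75 − 0.675 = 0.075 (r = 0.5) to 0.75 − 0.60 = 0.15 (r = 0), or 10% to 20% of 0.75. This is one scenario. If instead mainly placebo participants left for lack of effect and were imputed like placebo participants who stayed, placebo would look better than it was and the error would run the other way.

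**The case against.** Much of the case against a stronger claim stands.

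- **Discretion.** A reader might infer that every non-compliant or deviating participant is removed. The text leaves removal to the investigator, and the per-protocol set's own exclusions for compliance and prohibited drugs would be largely redundant if all such participants had already gone. Loss is possible, not certain. Discretion exercised case by case after randomisation is itself undesirable, although blinding of investigators limits how far it can follow treatment arm.
- **Imputation.** A reader might also infer that the protocol imputes leavers as if they had continued. It does not say so. That is the usual default, and the assumption may properly be set in a separate analysis plan, so its absence here is not a fault.
- **Analysis set.** Nor does the primary comparison become one among adherers. The FAS keeps anyone with one post-dose evaluation, and their week-2 and week-4 values enter the model.
- **Unavoidable losses.** Item 2 also covers participants who ask to leave, and item 3 those who cannot be traced. A protocol sentence may not recover them. Item 6 uses overall compliance, whose last check is at week 6.
- **Power and estimand.** Retaining leavers raises power only if they keep most of the benefit. Using observed values after drug is stopped also asks a somewhat different question from the one on which the sample size was built.

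These points narrow the finding but do not remove it. For a participant removed before week 6 who would have kept the diary going, the value is lost through the protocol's own rule, and no later analysis choice brings it back.

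**Conclusion.** The point holds in limited form and should be addressed. The protocol does not distinguish stopping drug from leaving the trial, and it plans no CDS collection after removal. Where removal comes before week 6, it creates avoidable missing data in the primary endpoint for reasons tied to outcome, and methods that assume missing at random would not repair them.

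The size and direction of bias cannot be derived from the document. The protocol gives neither dropout by arm nor the outcomes of leavers, so the figure of 0.075 to 0.15 CDS points is an illustration resting on 20% leavers in each arm who keep none to half of the benefit. A reader might take the rise from 80% to 88% power as a reason for the change. The protocol does not support that, because it requires the full 0.75 in people off drug or deviating. Under the same 20% assumption, power is about 71% to 81%. The argument for the change is a valid comparison of the randomised groups.

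**What to change.** Amend Dropout and Early termination criteria as follows:

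- Leave the listed reasons for stopping study drug as they are. State that stopping drug, or deviating from the plan, is not withdrawal from the trial.
- Continue the cough diary and the scheduled visits to weeks 6 and 8 for everyone who does not withdraw consent. Record the date drug was stopped, other drugs taken and deviations.
- In Statistical analysis, use the observed week-6 CDS in the FAS whether or not the participant was still on drug, and impute only what is truly missing. Leave exclusions for compliance and prohibited drugs to the per-protocol set.

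While this section is open, item 6 needs reconciling with the rest of the protocol. It names YGJ and PWS groups, which are not arms of this trial, and its 70% differs from the 75% in the per-protocol definition.

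The cost is a short amendment and continued follow-up of up to about 28 participants (20% of 138), using the existing diary and visits. The downside is that data collected off drug or under other drugs may dilute the effect to about 0.60 to 0.675 under the assumptions above. The sponsor should decide knowingly whether 69 per arm is still enough: with 20% leavers keeping no benefit, 86 per arm with week-6 data would be needed for 80% power.

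### The compliance dropout rule names two groups this trial does not have, and its 70% limit is not related to the 75% limit of the per-protocol set

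*Protocol*

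**What the plan says.** The protocol, under Dropout and Early termination criteria, lists conditions under which a participant "will be dropped out from the trial at the discretion of investigators". Item 6 applies "when it is judged that the effect evaluation of the clinical trial is not appropriate", the reason being that "the overall compliance with the investigational products is less than 70% in YGJ and PWS groups".

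The arms are described differently everywhere else. Procedure states: "Participants will be allocated to either the OJS plus SMS group or the placebo group in a 1:1 ratio". Randomization and Blinding agrees: "The allocation ratio was 1:1 for each intervention (OJS plus SMS) and control (placebo) group". The Synopsis and the Sample size table show the same two arms. The Abbreviation list contains neither YGJ nor PWS.

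Under Statistical analysis, "full analysis (FAS) set will be the primary analysis set in this trial", and the PP set is additional. The FAS requires randomisation and at least one efficacy evaluation after dosing; it has no compliance criterion. The PP set is described as those who completed without violating the protocol, "with compliance lower than 75%, taking prohibited medications, or presenting with serious adverse events".

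**The concern.** Item 6 is an operative rule: it decides who leaves the trial, not merely who leaves an analysis. A rule addressed to groups that do not exist gives sites no usable text. Some may read it as covering both arms, and others may set it aside or rely on the general discretion in items 7 and 8. Anyone dropped before week 6 has no complete diary for the primary endpoint, the change in cough diary score from baseline to week 6. Those values must then come from the mixed model and multiple imputation.

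The two compliance figures add to the doubt. Both bear on whether a participant took enough medication for efficacy to be assessed, yet one is 70% and the other 75%, with no word on why. Because the 70% stands in a sentence that names the wrong groups, one cannot be sure that it was chosen for this trial.

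The PP definition has two faults of its own. Its grammar places low compliers inside the set. It also removes participants for having a serious adverse event. That is a post-randomisation outcome which treatment may cause, so the exclusion conditions the PP comparison on a possible treatment effect.

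**Working it through.** **1. The groups.** Set side by side:

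| Place in the protocol | Groups named |
| --- | --- |
| Synopsis; Sample size; Procedure; Randomization and Blinding | OJS plus SMS; placebo |
| Dropout criteria, item 6 | YGJ; PWS |
| Abbreviation list | neither YGJ nor PWS |

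No reading of the document maps YGJ or PWS to an arm. Taken literally, item 6 covers 0 of the 138 planned participants.

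**2. The two limits in doses.** Procedure gives three administrations a day for 6 weeks. Assume exactly 42 days, with each administration counting once.

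- Scheduled doses: 3 × 42 = 126.
- 70% limit: 0.70 × 126 = 88.2, so below 70% means 88 doses or fewer (88/126 = 69.8%).
- 75% limit: 0.75 × 126 = 94.5, so below 75% means 94 doses or fewer (94/126 = 74.6%).
- Between the limits: 89 to 94 doses (70.6% to 74.6%).

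The week-6 visit has a window of 3 days either way. If dosing followed the visit:

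- 39 days: 117 doses, limits 81.9 and 87.75, band 82 to 87.
- 45 days: 135 doses, limits 94.5 and 101.25, band 95 to 101.

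The band is six or seven doses wide in each case.

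**3. What each limit decides.**

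| Compliance | Item 6, if it covered both arms | FAS | PP set, if low compliance is an exclusion |
| --- | --- | --- | --- |
| below 70% | may be dropped | in, if evaluated at least once after dosing | out |
| 70% to below 75% | not a ground for dropping | in, on the same condition | out |
| 75% or more | not a ground for dropping | in, on the same condition | compliance criterion met |

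The tiers are logically consistent. PP membership turns on the 75% alone. The 70% affects only who is withdrawn, and hence whose later data are missing.

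**4. The PP sentence.** Read as written: "PP sets were defined as participants who completed the trial without violating the protocol, with compliance lower than 75" per cent. Grammatically, the words on compliance describe members of the set. The sense must be exclusion, because the same list goes on to prohibited medication and serious adverse events.

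**5. The sample size.** Sample size gives a difference of 0.75, SD 1.4, power 0.8, two-sided 0.05 and dropout 20%.

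- n = 2 × (1.960 + 0.842)² × 1.4² / 0.75² = 2 × 7.85 × 1.96 / 0.5625 = 54.7, so 55 per group.
- 55 / (1 − 0.20) = 68.75, so 69 per group and 138 in total, as stated.

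No compliance limit enters this calculation. Withdrawals under item 6 would count towards the 20% allowance.

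**The case against.** The strongest reply is that the two figures serve different purposes. Item 6 is a discretionary withdrawal rule, and the 75% defines an analysis set. A withdrawal trigger looser than a PP criterion is coherent, as the tier table shows. This stands. A reader might infer that the two limits contradict each other, or that someone taking 89 to 94 doses is declared evaluable in one place and not in the other. The document supports neither: item 6 lists grounds for dropping and defines no evaluable population. What remains is that the tiers are nowhere stated.

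A reader might also infer that membership could be settled after the data are seen. That is not supported. Investigators, participants and outcome assessors are blinded, the PP figure is already fixed, and the discretion comes from the lead-in to the dropout list, not from the gap between 70% and 75%.

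It can be said that blinded sites could not apply an arm-specific rule anyway, and that items 7 and 8 let investigators withdraw participants on other grounds. Both are true, so the rule's failure does not leave sites without any means of acting. But this makes uneven application across sites more likely, and an analysis plan cannot repair a withdrawal rule that sites apply from the protocol.

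On serious adverse events, the set is only additional, it already requires completion (itself a post-randomisation condition), and the randomisation section allows the code to be disclosed after such an event. Unblinding might justify an exclusion, but the sentence excludes on the event itself. A participant who took every dose, completed every visit and was never unblinded would still be removed.

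**Conclusion.** The point holds, with limited reach. Item 6 is wrong as written: its groups do not exist in this trial. The 70% and 75% limits are different and unreconciled, but not contradictory. The PP sentence is garbled, and its serious-adverse-event criterion is poorly chosen.

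The effect is confined to withdrawals, the missing data they cause, and the additional PP analysis. The FAS definition, its status as primary set and the 69 per group are untouched. The loss of week-6 diary data depends on timing. Compliance is checked at weeks 2, 4 and 6, and item 6 does not say when overall compliance is judged. If only at week 6, the week-6 diary would normally already be in hand, and mainly the week-8 visit would be lost.

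The band of 89 to 94 doses rests on 42 days and one count per administration. How many participants would fall in it cannot be estimated from the document. It is tempting to conclude that item 6 was carried over from another protocol; the document does not establish that, and the finding does not need it.

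**What to change.** 1. In item 6, correct the group names so that they refer to the arms of this trial.
2. Reconcile the 70% and 75% figures, or state explicitly how the withdrawal rule and the PP criterion relate. Do this before unblinding and word both places to match. This review takes no view on which figure is right, or on whether they should be equal.
3. Reword the PP definition so that low compliance is plainly an exclusion.
4. Base PP exclusions on protocol deviations, and remove the occurrence of a serious adverse event as a criterion in itself.

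The cost is wording in two sections. No data collection, sample size or primary analysis changes. Since the protocol was authorised by the ministry and approved by five review boards, the corrections would presumably go through the usual amendment route, and sites would need to be told of the corrected item 6.
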